#### Data recording

Clinical data will be recorded at the intervals described above. For routinely collected clinical data hospital notes and charts will be the source documents. For study-specific data the case report form (CRF) will be the source document.

#### Data quality

The Chief Investigator (CI)/Study Lead (SL) will provide training to site staff on trial processes and procedures. CRF completion and data collection will be the responsibility of the SL and designated team members. The clinical data management process will be governed by internal standard operating procedures (SOPs), designed to ensure adherence to International Conference on Harmonisation Good Clinical Practice (ICH GCP) guidelines.

### Statistical methods

All analyses will be undertaken by an independent biostatistician. The statistician will be blinded to treatment allocation. Analysis will be undertaken on an intention-to-treat basis. Continuous data will be checked for normality and presented as mean (standard deviation) or median (interquartile range). Categorical data will be presented as counts (percentages). Where data are continuous, they will be compared using Student’s *t* test or the Mann-Whitney U test as appropriate. Categorical variables will be compared using the chi-squared test. All tests will be two-tailed, and a *p* value <0.05 will be considered significant. For the primary outcome measure, change in EELI, a mixed-effects regression model will be used. The modelling methodology will follow that used in our previous trial of HFNO_2_ therapy [35].

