#### Sample size and study duration

This is a pilot study and as such no formal power calculation has been made. A convenience sample of 50 patients has been chosen based on anticipated recruitment rates and a feasible study duration.

Given our institution’s current workload, approximately two patients per week will meet the inclusion/exclusion criteria. Allowing for a 50% consent rate, and 10% loss to long-term follow up, recruitment could be completed in 54 weeks. Given the final follow up occurs 6 weeks post-operatively, data collection may be completed by week 60. Data analysis and write up of results will take an additional 12 weeks. Therefore, completion of the study is expected within an 18-month time frame.

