#### Allocation

Randomisation will be achieved using a computer-generated random number table, with an allocation ratio of 1:1. Allocation concealment will be maintained using sequentially numbered sealed opaque envelopes. Envelopes will be prepared by an independent person. Each envelope will contain a unique patient identifier code and will allocate the participant to either the intervention group (HFNO_2_) or the control group (standard oxygen therapy). Randomisation will occur post-operatively on admission to the ICU. The theatre team will be blinded to the allocation. Due to the research design, neither the individual collecting data nor the patient can be blinded to treatment allocation.

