#### Outcome measures

Primary and secondary outcome measures are summarised in Table 2. The primary outcome measure is ∆EELI from baseline to 6 h post-return to ICU.

**Table 2 Tab2:** Summary of primary and secondary outcome measures

Phase	Outcome measure	Timing	
Day 0	Change in end expiratory lung impedance (∆EELI)	6 h	Primary outcome
Day 0	Change in end expiratory lung impedance (∆EELI)	15 min, 60 min, and 3 h	Secondary outcomes
	Change in Tidal impedance variation (∆VARt)	0, 60 min, 3 h, and 6 h	
	Change in oxygenation (PaO_2_/FiO_2_)		
	Change in arterial CO_2_ (PaCO_2_)		
	Change in respiratory rate		
	Change in modified Borg dyspnoea score		
	Requirement for escalation of O_2_ therapy		
Discharge	Length of ICU stay	Day 2–3	
	Re-admission to ICU		
	Length of hospital stay		
	Diagnosis of a respiratory complication		
Follow up	Hospital re-admission	Week 6	
	Diagnosis of a respiratory complication		

*EELI* end expiratory lung impendence, *PaO*_*2*_*/FiO*_*2*_ arterial partial pressure of oxygen/fraction of inspired oxygen; *PaCO*_*2*_ arterial partial pressure of carbon dioxide

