### Data collection, quality and management

#### Time points

Pre-operative refers to the period after recruitment, but before surgery and before randomisation. Pre-operative data collected include:Patient demographics (age, gender, height and weight)Modified Borg dyspnoea score of 0 = no dyspnoea to 10 = maximal dyspnoea [44]Co-morbidity data (including smoking history)Baseline physiological parameters (heart rate, blood pressure, respiratory rate, peripheral oxygen saturation)

Baseline refers to the period after surgery and before randomisation. All patients will return from theatre after being extubated by the responsible anaesthetist and after receiving 6 L/min of 0_2_ via a Hudson mask. Baseline data collected include:EIT file recordingArterial blood gas analysis▪ Arterial partial pressure of oxygen (Pa0_2_)▪ Arterial partial pressure of carbon dioxide (PaC0_2_)▪ Calculated Pa0_2_/Fi0_2_ ratioPhysiological parameters (as above)Modified Borg dyspnoea score (as above)Pain score▪ Numerical scale where 0 = no pain and 10 = maximal painOperative data▪ Type of operation preformed▪ Duration of operation▪ Any related complicationsGeneral anaesthesia data▪ Type of anaesthesia administered▪ Amount of analgesia given▪ Any related complications

After baseline data have been recorded, randomisation will occur - T0 refers to this point.

T15, T60 and T3 refer to 15 min, 60 min, and 3 h after T0, respectively. Data collected include:EIT file recordingArterial blood gas analysisPhysiological parametersModified Borg dyspnoea scorePain score

T6 refers to 6 h after T0. Data collected include all data from the above time point in addition to:Data on clinical course, need for oxygen titration or escalation of therapy

Discharge refers to the day of discharge from the hospital. Discharge data collected include:Hospital length of stayPhysiological parametersData on clinical course, need for oxygen titration or escalation of therapyICU re-admissionData on the incidence of PPCs

PPCs are defined in this study as any pulmonary abnormality, disease or dysfunction that adversely affects the clinical course of a patient in the post-operative period. This includes mild, moderate or severe respiratory failure, acute respiratory distress syndrome (ARDs) new onset bronchospasm, new pulmonary infiltrates on chest x-ray, pulmonary infection and the presence of new plural effusions, atelectasis, cardiopulmonary oedema or pneumothorax [45].

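### Secondary change scores are compared without baseline as a covariate, and binary outcomes by chi-squared with no alternative for small counts: a minor, cheap improvement

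*Protocol article*

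**What the plan says.** The Statistical methods section of the protocol article gives one general rule for everything except the primary outcome. Continuous data are compared by Student's t "test or the Mann-Whitney U test as appropriate. Categorical variables will be compared using the chi-squared test". Tests are two-tailed, and a p "value <0.05 will be considered significant". No covariate is named and no alternative to chi-squared is given. A mixed-effects regression is assigned to the primary outcome only.

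Table 2 (Outcome measures) words the continuous physiological secondary outcomes as changes: tidal impedance variation, PaO2/FiO2, PaCO2, respiratory rate and, for example, "Change in modified Borg dyspnoea score". Its binary outcomes are escalation of oxygen therapy, ICU re-admission, hospital re-admission and diagnosis of a respiratory complication.

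Under Time points, "Baseline refers to the period after surgery and before randomisation", and the data collected then include the EIT file, blood gases, physiological parameters and the Borg score. These measurements are repeated up to 6 h. The Intra-operative management section limits the baseline blood gas to patients who have an arterial line.

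On size, "A convenience sample of 50 patients has been chosen based on anticipated recruitment rates and a feasible study duration", and "This is a pilot study and as such no formal power calculation has been made". Allocation is 1:1.

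**The concern.** A pre-randomisation value is planned for each repeated physiological outcome. The stated two-sample tests use it only by subtraction, which fixes its weight at one whatever the correlation with follow-up. When that correlation is modest, the change score carries avoidable noise, and a chance baseline difference between arms passes into the treatment contrast.

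For binary outcomes the plan names one large-sample test for every count, without saying whether a continuity correction applies. Re-admission and escalation could be rare. With few events, whether the 0.05 threshold is crossed can depend on the software default.

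What is at stake is the precision and clarity of secondary results. The Study objectives section says the study's data, including complication estimates, will be used to design a larger trial.

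**Working it through.** **Inputs from the protocol.** Total sample 50 with 1:1 allocation, so 50/2 = 25 per arm. Planning allows for "10% loss to long-term follow up"; if 50 are randomised, 50 × 0.9/2 = 22.5 per arm remain at week 6. The two-sided level is 0.05. The only background rate for a respiratory complication is 37% (atelectasis, Background section). There is no power calculation to reproduce.

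**Assumptions.** The correlation r between baseline and follow-up, a treatment effect of 0.8 SD, the event counts in the examples, and equal SDs at baseline and follow-up.

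**1. Baseline as covariate.** In units of SD², and ignoring the small cost of estimating the slope:
- follow-up value alone: 1
- change score: 2(1 − r)
- baseline-adjusted (ANCOVA): 1 − r² = (1 − r)(1 + r)

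The ratio of ANCOVA to change score is (1 + r)/2, so the reduction is (1 − r)/2.

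| r | change score | ANCOVA | reduction | power at 25 per arm, 0.8 SD: change v ANCOVA |
|---|---|---|---|---|
| 0.3 | 1.40 | 0.91 | 35% | 66.7% v 84.3% |
| 0.5 | 1.00 | 0.75 | 25% | 80.7% v 90.4% |
| 0.7 | 0.60 | 0.51 | 15% | 95.5% v 97.7% |

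Below r = 0.5 the change score is noisier than the follow-up value alone (1.4 against 1.0 at r = 0.3). At r = 0.9 the reduction is only 5%.

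**2. Chance imbalance.** The standard error of the baseline difference between arms is √(2/25) = 0.28 SD. An imbalance of that size moves the change-score contrast by (1 − r) × 0.28, which is 0.14 SD at r = 0.5. ANCOVA removes this shift.

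**3. Chi-squared with small counts.** The expected number of events per arm is 25 × the pooled rate, so it is below 5 when the rate is under 5/25 = 20% (5/22.5 = 22% with the week-6 number). At 37% it is 25 × 0.37 = 9.25. For 4/25 against 0/25:
- Pearson: 50 × (4 × 25 − 0 × 21)²/(25 × 25 × 4 × 46) = 500,000/115,000 = 4.35, p = 0.037
- Yates: 50 × (100 − 25)²/115,000 = 2.45, p = 0.118
- Fisher: p = 0.110

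For 6/25 against 1/25 the three p-values are 0.042, 0.103 and 0.098.

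**4. Error rate of Pearson's test.** Enumerating all tables at 25 per arm gives an exact size of 1.2% at a 4% event rate, 4.9% at 10%, 5.5% at 20%, 5.8% at 37%, and at most 6.5% (at 50%).

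**5. Choosing between t and Mann-Whitney by a normality check.** In 10,000 simulated trials per distribution at 25 per arm, I used Shapiro-Wilk in each arm and the t test only if both passed. The two-sided error was 0.050 (normal), 0.047 (lognormal), 0.044 (exponential) and 0.048 (t with 3 df). On truly normal data the rule moved to Mann-Whitney in about 10% of trials.

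**The case against.** Three stronger readings are tempting, and the document does not support them.

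- **That baseline data are ignored or discarded.** Table 2 defines these outcomes as changes, so a test on them uses baseline. Both the change score and ANCOVA are unbiased under randomisation. What remains is a matter of efficiency, of a size that depends on r.
- **That the continuous p-values are fragile because a normality check picks the test.** The text ties that check to how data are presented; its use to select the test is a fair inference and no more. Even if it is used that way, step 5 shows the error rate staying near 5%. A chance switch between a mean and a rank comparison can make results harder to compare across time points, but that is a reporting nuisance.
- **That chi-squared seriously inflates false positives.** Step 4 shows that it does not. The test is adequate near the 37% rate, and the protocol's definition of pulmonary complications is broader than atelectasis. The 4 v 0 and 6 v 1 tables are illustrations, not forecasts.

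It can also be said that complication estimates will be reported as counts and percentages, which no choice of test affects, and that no decision hangs on a secondary p-value. Both points are fair and keep the severity low. Finally, a fallback for small counts is a detail often left to an analysis plan, and none is shown. That carries weight for the exact test. It carries less for the comparison as a whole, because the article states the tests outright, and an analysis plan that used others would depart from its published wording.

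**Conclusion.** The point holds as a minor one. The stated methods for continuous secondary outcomes leave out a covariate that the trial plans to collect, at a cost of 15% to 35% in variance for assumed r between 0.7 and 0.3. PaO2/FiO2 and PaCO2 can gain only in patients with a baseline arterial sample; length of stay has no baseline value and is unaffected. For binary outcomes the concern is confined to pooled rates below about 20%, where the verdict at 0.05 can depend on an unstated choice of variant. The protocol gives no rates for re-admission or escalation, so whether this will arise is not known. The primary outcome has its own model and is outside this point.

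**What to change.** Analyse tidal impedance variation, respiratory rate, Borg score and, where an arterial line gives a baseline sample, PaO2/FiO2 and PaCO2 by baseline-adjusted regression. This can be ANCOVA at each time, or a mixed model with the baseline value as covariate and an arm-by-time term. Report estimates with 95% CIs. State these terms explicitly, because the article does not spell out the covariates of the primary model and refers to a previous trial for its method.

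For binary outcomes, report the risk difference with a 95% CI, and use an exact test where any expected count is below 5.

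The cost is analysis wording and slightly more programming; no extra data or patients are needed. The exact test is conservative: at 25 per arm Fisher's true size is 0.9% at a 10% event rate and 2.2% at 20%. P-values for sparse binary outcomes will therefore be less favourable, which is a further reason to put the weight on the interval.

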### Adverse events (AE) and serious adverse events (SAE)

AEs and SAEs will be monitored and reported to the Human Research Ethics Committee (HREC). The AE reporting period for the trial begins at randomisation and ends 48 h after randomisation. The CI or their delegated investigator is responsible for recording and reporting of AEs observed during the study period. Events occurring because of the patient’s underlying condition will not be reported as an AE. The CI must assess severity, seriousness, causality and expectedness of any AEs in keeping with regulatory requirements. All events meeting the definition of an SAE should be notified to the CI within 24 h of occurrence. Follow-up information should be sought and submitted as it becomes available. The follow-up information should describe whether the event has resolved or persists, if and how it was treated and whether the patient continues in the study or has been withdrawn from treatment. Once received, seriousness, causality and expectedness will be confirmed by the CI (or delegated SL). SAEs will be notified to the Research Ethics Committee (REC) within 72 h.

## Discussion

HFNO_2_ has become more accessible in recent years and is now commonplace in the ICU, emergency departments and operating theatres. HFNO_2_ therapy is minimally invasive, safe and has few contraindications. We aim to test the hypotheses that respiratory support, in the form of HFNO_2_, leads to an increase in EELV, conferring a reduction in the incidence and duration of post-operative atelectasis.

HFNO_2_ provides a degree of positive airway pressure, which may aid alveolar recruitment and prevent de-recruitment [35, 36]. Corley et al. showed a significant increase in EELV in patients with respiratory compromise, treated with HFNO_2_, following cardiac surgery. This increase in EELV was greater in those with a higher BMI, suggesting a benefit in this cohort.

Trial recruitment began in April 2017 at St Andrews War Memorial Hospital, Brisbane and is anticipated to be completed by the end of April 2018. We aim to publish the results as a single manuscript. It is anticipated that the results of this study will be used to inform the operational design and feasibility of a larger randomised controlled trial.

### Trial status

This trial is ongoing and actively recruiting.

Date recruitment started, 3 April 2017.

Date of anticipated completion, 31 June 2018.

## Abbreviations

AE: Adverse event
AUD: Australian dollar
BMI: Body mass index
CI: Chief Investigator
CRF: Case report form
EELI: End expiratory lung impendence
EELV: End expiratory lung volume
EIT: Electrical impendence tomography
FiO_2_: Fraction of inspired oxygen
GA: General anaesthesia
HFNC: High flow nasal cannulae
HFNO_2_: High flow nasal oxygen
ICU: Intensive care unit
OHS: Obesity hypoventilation syndrome
OSA: Obstructive sleep apnoea
PaO_2_,: Arterial partial pressure of oxygen
SAE: Serious adverse event
SL: Study Lead
SOPs: Standard operating procedures
SPIRIT: Standardised Protocol Items: Recommendations for Interventional Trials
SpO2: Peripheral oxygen saturation
Vt: Tidal volume
